# Implementation strategy for an antibiotic stewardship bundle to promote optimal treatment choices in neonates with suspected early-onset sepsis (Protect-Neo): a study protocol for a multicentre, prospective interrupted time series and before-after study

**DOI:** 10.1136/bmjopen-2025-103368

**Published:** 2025-11-04

**Keywords:** INFECTIOUS DISEASES, Antibiotics, NEONATOLOGY, Sepsis

## Abstract

**Abstract:**

**Background:**

Several antibiotic stewardship interventions have been proven effective and safe for reducing the high number of antibiotic prescriptions in late preterm and term neonates at risk of early-onset sepsis (EOS). For successful translation of EOS interventions to clinical practice, implementation strategies should be employed targeting stakeholders. The primary aim of this study is to assess the impact of implementing an antibiotic stewardship bundle, including the EOS calculator, procalcitonin-guided therapy and intravenous-to-oral switch therapy on antibiotic exposure for EOS in Dutch secondary hospitals. Secondary aims are to examine additional clinical outcomes and implementation outcomes.

**Methods and analysis:**

We will conduct a multicentre, prospective implementation study with interrupted time series and before-after analyses at the paediatric or specialised neonatal departments of 11 Dutch secondary hospitals and their surrounding neonatal care networks. A multimodal implementation strategy, designed using Implementation Mapping, is employed to facilitate implementation. The study population is twofold: (1) neonates born at 34 weeks of gestation or later with suspected EOS that will receive intervention-related care and (2) paediatricians, paediatric residents, neonatal nurses, maternity nurses and parents who are the focus of the implementation strategies. The primary outcome is days of antibiotic therapy per 1000 live-born neonates, which will be evaluated using interrupted time series analysis as well as before-after comparison. Secondary clinical outcomes will be assessed by comparing clinical data from the 12 months pre-implementation and post implementation. Implementation outcomes are adoption, fidelity, feasibility and acceptability of the interventions and fidelity and appropriateness of the implementation strategies. Implementation outcomes will be assessed using both qualitative and quantitative methods, including surveys, individual interviews and focus group interviews. A mixed-methods approach will be used to integrate clinical and implementation outcomes.

**Ethics and dissemination:**

The Medical Ethics Committee United (MEC-U) declared (reference: W24.132) that this study does not fall under the Dutch Medical Research Involving Human Subjects Act (WMO). Subsequently, ethical approval was granted by the Scientific Committee of the Franciscus Hospital (T110). The scientific committees of all participating sites adopted this decision and granted permission for local conduct of the study. As electronic health record data are sampled retrospectively and anonymously, a waiver of consent was given to collect these data. Informed consent will be obtained from participants completing surveys or taking part in interviews and focus group discussions. The findings will be disseminated through journal publications and conference presentations. Furthermore, practice and policy recommendations will be collaboratively developed with partner organisations.

**Trial registration number:**

NCT06845332.

STRENGTHS AND LIMITATIONS OF THIS STUDYThis study utilises implementation strategies that were systematically developed via Implementation Mapping, based on comprehensive stakeholder input.The study’s practical, real-world approach reflects daily clinical practice, enhancing applicability outside controlled research settings.Implementing three interventions simultaneously allows insight into their interaction and combined effects.Automated extraction of data through Business Intelligence units limits the capture of detailed patient-level data.Lack of randomisation restricts causal conclusions, but the mixed-methods approach provides valuable insights into the impact and appropriateness of the strategies.

## Introduction

 Empirical treatment of neonates with suspected early-onset sepsis (EOS) largely contributes to the widespread use of intravenous antibiotics and hospitalisation in the first days of life.^1^,^3^ Given the increasing knowledge on adverse short- and long-term effects of early antibiotic use and the rising relevance of delivering appropriate care, there is a clear need to implement evidence-based strategies that focus on considerate use of antibiotic therapy and stimulate patient-centred care.^4^,^8^ This is especially evident given that current antibiotic prescription rates are disproportionate to the actual incidence of culture-proven EOS, highlighting the opportunity to optimise antimicrobial use.^1 9^

Recently, several antibiotic stewardship interventions have been studied to answer this need, intervening at different stages of managing neonates at risk for EOS.^10^,^14^ Three interventions with high-quality evidence for late preterm and term neonates are the EOS calculator, procalcitonin (PCT)-guided therapy and intravenous (IV)-to-oral switch therapy. First, utilisation of the EOS calculator, developed by Kaiser Permanente, has shown to reduce up to 44% of antibiotic prescriptions in neonates at increased risk of EOS compared with the conventional risk categorisation approach.^10 15 16^ Second, a PCT-guided treatment regimen showed the potential to significantly reduce duration of empiric antibiotic treatment in neonates at low or medium risk of infection.^12^ Third, in neonates in which bacterial infection cannot be ruled out, despite a negative blood culture, switching from IV to oral antibiotics after 2 days (IV-to-oral switch therapy) was found to be as safe and effective as a 7-day intravenous treatment regimen.^11 17^ These interventions promote considerate use of antibiotics and patient-friendly care, ultimately improving the quality of life of neonates and their families. Additionally, reducing hospitalisation may contribute to cost savings in healthcare and increase the availability of scarce hospital beds.^18^,^20^

However, all aforementioned interventions are not yet integrated into the Dutch national guideline on EOS management, which was most recently revised in 2017.^21^ Some Dutch hospitals already adopted one or more of the antibiotic stewardship interventions independently, but they are not applied in the vast majority. To integrate novel evidence into daily practice, active implementation should take place that carefully considers determinants influencing its application, including perspectives of all stakeholders.^22 23^ One of the challenges in the transition from evidence to practice is that most clinical interventions are researched primarily in controlled settings, yielding type 1 and 2 evidence on disease aetiology, burden and intervention effectiveness. As a result, there is limited type 3 evidence on how these interventions function in real-world environments, making it unclear what should be targeted for effective implementation.^24^ Moreover, since interventions are usually studied individually, little is known about how they interact with other evidence-based approaches for the same disease. Regarding neonatal antibiotic stewardship, several studies have reported the effect of implementing antibiotic stewardship interventions, yet reported mainly the impact on antibiotic prescription rates rather than data on the implementation context and strategies.^25 26^ The few studies that did emphasise implementation strategies were conducted at neonatal intensive care units with Level IV facilities.^27 28^ In contrast, most Dutch late preterm and term neonates at increased risk of EOS are born and treated in secondary hospitals (Level I–II facilities) and receive care in collaboration with the obstetric department and primary neonatal care.

Therefore, the primary aim of this study is to assess the impact of the strategy to implement an antibiotic stewardship bundle (the EOS calculator, PCT-guided therapy and IV-to-oral switch therapy) on antibiotic exposure for EOS in Dutch secondary hospitals. Secondary aims are to assess additional clinical outcomes and implementation outcomes, including the acceptability, feasibility and fidelity of the interventions, as well as the appropriateness of the implementation strategies.

## Method

### Study design

This study is part of the Protect-Neo implementation project and focuses on the implementation and evaluation phase of the project. We will perform a multicentre, prospective, interrupted time series (ITS) and before-after implementation study. Mixed methods will be used to integrate clinical outcomes with implementation outcomes. The study runs from January 2024 to June 2026 and comprises a 9-month implementation period followed by a 12-month post implementation period during which data are collected. In addition, a 12-month pre-implementation period (January–December 2023) provides baseline data for the comparison of clinical outcomes (figure 1). The implementation period is divided into two distinct phases: a 6-month preparation phase (eg, change of local protocols, informing stakeholders, lobbying for equipment), followed by a 3-month active implementation phase (educational sessions, spread of informative materials, etc.).

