### Analysis

#### Primary outcome

An ITS analysis will be conducted to compare trend of overall DOT (all types of antibiotic agents) per 1000 live births pre- and post-intervention. The ITS will have at least four data points in the pre-implementation period and four datapoints in the post implementation period, based on quarterly intervals. If the number of cases allows dividing the data into more datapoints, this may be considered. To account for potential clustering of observations within hospitals and potential differences between hospitals, we will apply a mixed-effects segmented regression analysis for ITS (‘joinpoint regression’) with DOT as dependent variable and random intercept for each hospital. Also, we will include random slopes for the post-intervention trend, allowing hospitals to differ not only in baseline DOT levels but also in how they respond to the implementation. Fixed effects include intervention phase (pre/post) and segmented time after the intervention to estimate both immediate level changes and changes in trend. Confounders, including the number of positive blood cultures, mean gestational age and mean birth weight will be included as time-varying covariates. Depending on data availability, we may also examine trends during the intermediate implementation phase to explore changes during this transition period as secondary analysis. Autocorrelation of residuals will be checked by using the Durbin-Watson test, and if present, corrected. Results will be reported as adjusted changes in level and trend, with 95%CIs, reflecting both pooled effects and between-hospital variability. Additionally, a before-after comparison will be performed using a t-test or Mann-Whitney U test, for both overall DOT and DOT per individual antibiotic agent.

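### The stated periods fill 21 of the study's 30 months, leaving 9 to 18 months between a one-year baseline and the post period, which makes the ITS level change imprecise or exposes it to background trend

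*Protocol article*

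**What the plan says.** Under Study design, the Protocol article gives the calendar as "The study runs from January 2024 to June 2026 and comprises a 9-month implementation period followed by a 12-month post implementation period". The nine months split into "a 6-month preparation phase (eg, change of local protocols, informing stakeholders, lobbying for equipment), followed by a 3-month active implementation phase", so preparation lies inside them. The baseline is the same for every site: "a 12-month pre-implementation period (January–December 2023) provides baseline data for the comparison of clinical outcomes". The text gives no calendar dates for the implementation or post period. It refers to Figure 1 for the timeline, and that figure is not shown in the copy reviewed.

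Under Analysis, Primary outcome: "The ITS will have at least four data points in the pre-implementation period and four datapoints in the post implementation period, based on quarterly intervals". It adds: "If the number of cases allows dividing the data into more datapoints, this may be considered". The fixed effects named are phase and time since the intervention; a baseline time term is not listed. Trends in the intermediate phase may be examined if data allow, as a secondary analysis. A before-after test on DOT is also planned. The section on electronic health record (EHR) data limits sampling of treated neonates, and the count of live births, to the two outer periods.

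**The concern.** An ITS level change compares the first post-period value with the value the baseline trend predicts for that date. Here the prediction rests on as few as four quarters, carried across at least three quarters that are outside the primary analysis. The uncertainty in the slope is multiplied by that distance.

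Leaving the slope out removes the extrapolation. Any decline already under way between 2023 and the post period is then credited to the implementation strategy. The Introduction says some Dutch hospitals have already adopted one or more of the interventions on their own, so a background decline is plausible.

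Because the text leaves nine months unassigned, a reader cannot tell how long the gap is or build the time axis of the primary analysis.

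**Working it through.** **Calendar.** January 2024 to June 2026 is 12 + 12 + 6 = 30 months. The stated parts are 9 + 12 = 21, leaving 9.
- If implementation starts in January 2024, it ends in September 2024 and the post period is October 2024 to September 2025. The gap after the baseline is 9 months (3 quarters).
- If the post period ends in June 2026, it starts in July 2025 and implementation runs October 2024 to June 2025. The gap is 18 months (6 quarters).

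**Inputs from the Sample size section.** 3.8% of live births treated; 68.5% of courses last 2 days and 31.5% last 7 days; about 2500 births per hospital per year (range 1000 to 3500). Study setting gives 11 hospitals.
- Plan's own figure: 0.685 × 38 × 2 + 0.315 × 38 × 7 = 135.85, which reproduces the stated 136.
- Target drop: 136 − 60 = 76. Minimum relevant drop: 135 − 121.5 = 13.5.

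**Sampling SD per quarter.**
- Mean of squared days per birth: 0.038 × (0.685 × 4 + 0.315 × 49) = 0.6907.
- Variance: 0.6907 − 0.13585² = 0.672.
- Births per quarter: 11 × 2500 / 4 = 6875.
- SD = 1000 × √(0.672 / 6875) = 9.9 DOT per 1000.

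**SE of the level change with a baseline slope** (pooled least squares, change taken at the first post quarter). For four quarterly points the sum of squares of time is 5. With g gap quarters the variance, in units of the quarterly variance, is

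[1/4 + (2.5 + g)²/5] + [1/4 + 1.5²/5]

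The first bracket is the extrapolated baseline; the second, 0.70, is the fitted post value.

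| Gap | Variance factor | SE | 95% CI | Power, drop of 76 | Power, drop of 13.5 |
|---|---|---|---|---|---|
| none | 1.50 + 0.70 = 2.2 | 14.7 | ±29 | >99% | 15% |
| 9 months | 6.30 + 0.70 = 7.0 | 26.2 | ±51 | 83% | 8% |
| 18 months | 14.70 + 0.70 = 15.4 | 38.8 | ±76 | 50% | 6% |

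Power is two-sided at 5%, normal approximation. Over 1000 to 3500 births per hospital, power for the drop of 76 runs from 45% to 93% with a 9-month gap and from 24% to 64% with 18 months. Monthly points give SEs of 24.6 and 36.6, so finer intervals add little.

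**Without a baseline slope.** The factor is 0.25 + 0.70 = 0.95 and the SE is 9.9 × √0.95 = 9.6, whatever the gap. The cost is bias. As an assumption, not a figure in the article, take a background decline of 5% a year, or 6.8 DOT per 1000.
- The baseline midpoint and the first post quarter are 16.5 months apart (9-month gap) or 25.5 months apart (18-month gap). The false level drop is 6.8 × 16.5/12 ≈ 9 or 6.8 × 25.5/12 ≈ 14. A decline of 10% a year doubles these to about 19 and 29.
- For the before-after test the period midpoints are 21 or 30 months apart, giving about 12 or 17 at 5% a year.

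**Effect of a longer baseline** (9-month gap kept).
- Eight quarters: 1/8 + 7.5²/42 + 0.70 = 2.16, SE 14.5.
- Twelve quarters: 1/12 + 9.5²/143 + 0.70 = 1.41, SE 11.8.
- Late start with three usable 2024 quarters (seven baseline quarters, gap of three): 1/7 + 7²/28 + 0.70 = 2.59, SE 15.9 instead of 38.8.

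At SEs of 15.9, 14.5 and 11.8, power for 13.5 is about 14%, 15% and 21%; for 76 it exceeds 99%.

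**The case against.** A reader might infer that the dates contradict each other outright. The documents do not show that. Saying that a study comprises two periods need not mean they fill its whole window. A survey one year after active implementation, 28-day follow-up and close-out could occupy part of the remaining time, and Figure 1 may settle it. Staggered or late starts are nowhere stated, so the 18-month case is only what the dates allow. What stands is that the text leaves nine months unplaced, and that even the shortest reading leaves nine months between the two segments.

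A reader might also infer that the ITS level change is close to uninformative. That measures the interval against 13.5, which is the smallest drop called relevant; the goal is a drop of 76. With a 9-month gap, ±51 excludes zero for an estimated drop of that size. Nor is the gap the main reason a 10% drop escapes detection: power is only 15% with no gap at all.

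It would be too strong to call the intervening months unobserved, since the intermediate phase may be analysed. That analysis is optional and secondary, so it does not support the primary estimate.

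Finally, no baseline slope is named, and the before-after test needs none. Both points are fair. They replace imprecision with exposure to background trend, the weakness an ITS is meant to address.

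**Conclusion.** The point holds as a design improvement and a request to reconcile dates. The text accounts for 21 of 30 months, and the primary ITS has a gap of at least 9 months after a one-year baseline. With a baseline slope, a 9-month gap raises the SE of the level change about 1.8-fold (14.7 to 26.2) and an 18-month gap about 2.6-fold (to 38.8). Power for the target drop falls from above 99% to about 83% or 50%. Without a slope the estimate is tighter but cannot separate the strategy from background change.

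These figures are best cases. They assume the article's own course mix, 11 × 2500 births, and sampling error only. Season, autocorrelation and hospital-specific slopes would widen every interval. The background decline of 5% to 10% a year is illustrative.

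**What to change.** 1. Reconcile the dates, and state the calendar implementation and post periods, by site if starts are staggered.
2. Include a baseline time term in the segmented model and say so.
3. Extend the automated EHR and live-birth extraction one to two years before 2023 where records allow, and run it without a break through the implementation period.
4. Model the nine implementation months as their own segment. Count 2024 months as baseline only where they precede a site's documented preparation phase, because the study itself is dated from January 2024.

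The gain in precision comes from the longer baseline: with a 9-month gap, two or three years cut the SE from about 26 to about 15 or 12. Continuous data show when the change began. Moving from quarterly to monthly points is optional and adds little.

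The cost is a wider date range in an automated query, a larger data set, and a check for EHR or practice changes in the older years. The 10% drop will remain hard to detect through the level change, and the report should not present that estimate as able to rule it in or out.

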**Figure 1 F1:**
[figure not shown]
Implementation timeline.

### Study setting and population

The study is conducted at the paediatric or specialised neonatal departments of 11 Dutch secondary hospitals and their surrounding primary neonatal care networks, consisting of obstetric practices and maternity care services. In the Netherlands, neonates at risk for EOS are initially managed either in obstetric wards (Level I) or neonatal wards (Levels II–IV), depending on their age and clinical condition. Most late-preterm and term neonates receive care in secondary hospitals (Level I–II facilities). Following discharge, continuity of care is provided by midwives, maternity nurses and general practitioners. Midwives hold medical responsibility for the mother and clinically well-appearing neonates during the first 10 days postpartum, with support from maternity nurses in the home setting. In cases where neonates continue oral antibiotic therapy at home, medical responsibility remains with the paediatrician, while supported by primary care.

Participating sites were purposively sampled covering various Dutch regions to create a proper reflection of region-bounded differences in organisation of care. The study population is twofold: (1) neonates born at 34 weeks of gestation or later with suspected EOS that will receive care associated with the interventions and (2) paediatricians, paediatric residents, nurse practitioners, neonatal nurses, maternity nurses and parents who are the focus of the implementation strategies. Other involved professionals are pharmacists, microbiologists, midwives, gynaecologists and gynaecologic residents.

### Evidence-based antibiotic stewardship interventions

#### EOS calculator

The EOS calculator, which was developed by researchers of Kaiser Permanente, is applicable to neonates born at 34 weeks of gestation or later and can be used within the first 24 hours after birth.^10^ In this implementation project, it is advised to apply the EOS calculator to all neonates with increased risk of EOS, based on the presence of at least one risk factor or clinical symptom as specified in the current Dutch Society of Paediatrics’ guideline ‘Prevention and treatment of early onset neonatal infections’.^21^ The EOS calculator uses information on regional incidence and five maternal factors combined with the clinical evaluation of the neonate to assess individual EOS risk. The calculator then provides recommendations on the need for clinical observation using repeated evaluation of vital parameters, a blood culture and start of empirical intravenous antibiotics. In line with the protocol of the Dutch randomised controlled trial on EOS calculator safety and effectiveness, some deviations or clarifications have been made to the original EOS calculator’s approach in this study’s clinical protocol.^29^ First, the EOS calculator’s recommendation to obtain a blood culture and perform clinical observations is replaced with clinical observations only. This deviation reflects usual practices in the Netherlands, where obtaining a blood culture without subsequent antibiotic administration is uncommon. Second, evaluation of vital parameters is done every 3 hours instead of 4 hours, according to current Dutch workflows. Third, the EOS calculator gives no specific timeframe for observations in the ‘routine vitals’ recommendation, which is up to own interpretation. In this study’s clinical protocol, the duration has been standardised at 24 hours. For this implementation project, the EOS calculator is chosen over a 48-hour serial clinical examination approach, that also has the potential to significantly reduce antibiotic prescriptions, but demands more resources.^30^ The decision was based on the EOS calculator’s stronger evidence for reducing unnecessary antibiotic use, as well as logistical considerations regarding the demand for more staff and room capacity due to longer duration of the observation period of serial clinical examinations.

